### Trial management group

The Trial Management Group (TMG) is composed of a chairperson, vice chair, trial statistician, trial manager and 12 of the principal investigators. The TMG is responsible for approval of the trial design, reviewing and advising on trial recruitment, reviewing the final results, approving publications and approval of secondary studies.

### TMG executive group

The TMG Executive Group (TMG EG) is composed of the chairperson and vice chair of the TMG, one additional principal investigator, the trial statistician and the trial manager. The TMG EG is responsible for the conduct of the study, implementing decisions of the full TMG and ensuring that recruitment and data collection occur at an acceptable rate.

### Data monitoring and ethics committee

The Data Monitoring and Ethics Committee (DMEC) is composed of a clinical chair, an independent hepatologist and an independent statistician. The DMEC, in accordance with ICH-GCP guidelines is responsible for safeguarding the interests of trial participants, monitoring the main outcome measures including safety and efficacy, and monitoring the overall conduct of the trial. The DMEC receive, on a periodical basis, unblinded data on trial recruitment and data quality, outcome measures and safety data. The DMEC is required to assess emerging external evidence which might influence the ethical position of the trial. The committee is also expected to advise on any protocol modifications and whether the trial (or specific treatment groups) should be stopped early.

In agreement with the DMEC pre-planned interim analyses will be carried out after 200, 400 and 800 patients have reached the primary endpoint. Pre-specified stopping guidelines based on the Peto-Haybittle rule will be used at these interim looks. Namely, a two-sided *P* value <0.001 for harm or benefit (symmetrical stopping boundary) would indicate the DMEC recommend that the study or certain trial arms should be stopped. This method is being used because the treatments are already in use in practice and should evidence of harm or benefit arise, it needs to be convincing to ensure that others will change their practice accordingly. A *P* value of 0.001 is sufficiently small that the sample size does not need to be adjusted for these interim analyses [25].

### Ethical approval

Ethical approval was provided by the Wales Research Ethics Committee (Reference 09/MRE09/59) and a clinical trials authorisation issued by the Medicines and Healthcare products Regulatory Agency (MHRA) (Reference 11709/0227/001-0001).

## Discussion

An objective review of the literature on the treatment of alcoholic hepatitis inevitably encounters the controversy over the use of corticosteroids and the lack of confirmatory data on the use of pentoxifylline. Current international guidelines recommend the use of corticosteroids except in patients with sepsis, where pentoxifylline is the first choice of treatment [26]. These recommendations are attributed a lower grade of evidence acknowledging the controversies outlined above. Given the importance of this condition, a definitive large trial was required to settle the dilemma. If corticosteroids prove to be successful in this trial, it would still be reasonable to expect a mortality rate of 20% in treated patients based on the analysis of recent trials. There will remain an unmet medical need in this field, but at least future trials will legitimately use a steroid (or pentoxifylline) control arm based on solid evidence.

At the heart of the controversy over the use of corticosteroids is susceptibility to infection. Although 40 mg daily of prednisolone is considered a moderate dose, this group of patients is already highly susceptible to infection and corticosteroids are likely to exacerbate this problem. The emergence of infection during treatment is associated with a significant increment in the mortality rate [23].

Optimally, all patients enrolled in a treatment trial for alcoholic hepatitis would have a liver biopsy to confirm the diagnosis histologically [26]. However, the group of patients addressed by this study invariably have a coagulopathy and cannot be subjected to percutaneous biopsy. Transjugular liver biopsy is only available in specialist centres but alcoholic hepatitis is not usually considered as an indication for transfer to tertiary care. In addition even in specialist centres adequate histological samples may not be obtained in up to 4% of patients and biopsies may not be undertaken for a week after admission [27]. Previous studies which have a defined minimum level of bilirubin have confirmed histological features of alcoholic hepatitis in 98% of patients [28] and 96% of patients with acute-on-chronic liver alcoholic liver disease [29]. It was therefore decided to use strict clinical criteria including a minimum threshold of bilirubin to define the eligible patient group. This is a pragmatic decision which aligns the trial with the clinical practice that it should influence. Histology data will be collected from participating centres which have access to transjugular liver biopsy and used to validate the clinical criteria.

The primary endpoint of ‘mortality at 28 days’ was selected to align the study with previous trials in this area. As one previous trial showed important divergence between treatment groups after the 28-day time point arising due to increased rates of infection in the steroid arm, we believe that the 90-day mortality comparison will also be of interest to clinicians [30]. Previous studies have demonstrated that mortality beyond this time point is predominantly influenced by recidivism rather than the initial treatment choice [20].

Factorial 2 × 2 design is a well-established technique for concurrently assessing the benefit of two active treatments and is particularly appropriate in this situation where doubt exists over the efficacy of both medications. Factorial design trials are generally more powerful in detecting treatment effects unless there is a strong synergistic or inhibitory interaction between the two active medications. This is not considered to be likely in the current trial and it has rarely been observed in published trial results [31]. The two studies which have compared treatment with corticosteroids alone against the combination of corticosteroids and pentoxifylline have failed to demonstrate any difference in mortality rate between the two groups despite reasonable patient numbers. If the same is found in the current study then the assumption around no interaction between prednisolone and pentoxifylline may be challenged, in which case the trial will need to be analysed as a four-arm, which will inevitably reduce the study power and increase the width of any estimated confidence intervals.

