### Statistical considerations

#### Power calculation

In order to estimate the required trial sample size a power calculation was performed in nQuery Advisor using a two group continuity corrected χ^2^ test and the following parameters:

• Power = 90% (to allow for secondary outcomes)

• Two-sided significance level of 5%

• Estimated 28-day mortality rate in each treatment group is given in Table 1.

**Table 1 T1:** Estimated 28 day mortality rates for power calculation

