		**Pentoxifylline**		
		**Yes**	**No**	**Total**
Prednisolone	Yes	17%^a^ Group D	25% Group B	21%
	No	25% Group C	35% Group A	30%
	Total	21%	30%	

^a^Estimated assuming no interaction, that is multiplicative independent effects.

Based on a reduction in the 28-day mortality rate at the margins from 30% to 21%, a sample size of 513 per group of single agent *versus* no single agent would be required. Thus in total the trial would require 1,026 patients. We have allowed for an approximate 10% withdrawal/lost to follow-up rate and will therefore aim to recruit 1,200 patients to the study, with patients being evenly allocated to each treatment arm.

The sample size for this trial has not been powered to assess for any observed treatment interaction and in fact assumes no interaction between the two treatments (that is, that receiving prednisolone in addition to pentoxifylline does not change the effect of pentoxyfylline and *vice versa*). To be able to assess the interaction of two treatments, while keeping power at 90%, generally requires an increase in the sample size by four-fold [24]. As assessing the size of any interaction was not of primary interest as it was assumed to be small or non-existent, it was deemed appropriate to not power for assessing an interaction.

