### Statistical analyses

Analysis will be on the basis of intention to treat (ITT). In order to determine the efficacy of prednisolone, the 28-day mortality rate in those treated with prednisolone (that is, Groups B and D) will be compared with the mortality rate in control groups (Groups A and C). Similarly, the efficacy of pentoxifylline will be assessed by comparing the 28-day mortality rate in Groups C and D with the mortality rate in Groups A and B.

Although the study is not powered to detect a difference between two active treatments and single agent therapy, we will make this comparison for 28-day mortality rates. Logistic regression will be used to compare 28-day mortality between the treatment groups. The impact of pre-treatment variables such as gastrointestinal bleeding, sepsis or renal impairment on admission will be estimated by adding these covariates to the logistic regression analysis. Mortality rates at 90 days and 12 months will be compared using the same strategy. All analyses will be adjusted for the stratification variables and assessed at the two-sided 5% significance level. However, the impact of recidivism and hospital re-admission will also be assessed in relation to these outcomes.

Overall mortality will also be analysed as a secondary endpoint using the method of Kaplan-Meier and a cox-proportional hazards model adjusting for the same variables as explained above.

Rates of gastrointestinal bleeding, sepsis and renal failure will be summarised over time and by arm.

Stata for Windows (StataCorp) and SAS (SAS insititute inc) will be the statistical packages of choice. The study will be reported in accordance with the CONSORT (Consolidated Standards of Reporting Trials) statement.

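### The Discussion treats a null result for prednisolone alone versus the combination as grounds for doubting no interaction and moving to a four-arm analysis, but that comparison does not measure interaction

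*Protocol article*

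**What the plan says.** Under Statistical analyses, the efficacy comparisons are the two margins: B and D against A and C for prednisolone, and C and D against A and B for pentoxifylline. Power calculation sizes the trial on these margins. It explains no interaction as each drug having the same effect whether or not the other is given, and says the trial is not powered to test this.

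The factorial-design paragraph of the Discussion adds a caveat. It notes that the two studies of corticosteroids alone against corticosteroids plus pentoxifylline "have failed to demonstrate any difference in mortality rate between the two groups". It goes on: "If the same is found in the current study then the assumption around no interaction between prednisolone and pentoxifylline may be challenged". As the consequence of such a challenge it names a four-arm analysis, and it accepts that power would fall. The only observation named as grounds for the challenge is therefore a failure to separate B from D.

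Statistical analyses also concedes, of the combination against one drug alone, that "the study is not powered to detect a difference between two active treatments and single agent therapy".

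**The concern.** Interaction compares two simple effects: D v B (pentoxifylline given prednisolone) and C v A (pentoxifylline without it). The Discussion names only the first. If pentoxifylline does nothing, B equals D and A equals C. The named comparison is then null while the interaction is exactly zero, and the factorial analysis is fully valid. This is not a remote case, because the same paragraph justifies the design by doubt over whether either drug works.

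A null B v D can also arise by chance when pentoxifylline does work, since the comparison uses half the patients of a margin and is admittedly underpowered.

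What is at stake is mainly the prednisolone question. Leaving the margins would halve the numbers behind it, from about 600 v 600 to about 300 v 300 at full recruitment, for a reason that says nothing about whether the margins are valid.

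**Working it through.** **Inputs.** From Table 1 (Power calculation): A 35%, B 25%, C 25%, D 17%; margins 30% v 21%. Two-sided 5%, 90% power, "two group continuity corrected" chi-square test. 1,026 evaluable patients (1,026/4, about 256 per arm) and 1,200 recruited (1,200/4 = 300 per arm).

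**The plan's own figure.** With d = 0.09 and mean rate 0.255:

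n = [1.960·√(2·0.255·0.745) + 1.282·√(0.30·0.70 + 0.21·0.79)]² / 0.09² = (1.208 + 0.786)² / 0.0081, about 491.

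Continuity correction: (491/4)·[1 + √(1 + 4/(491·0.09))]², about 513. This matches the stated 513 per group.

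**What B v D can show.** On the log-odds scale, interaction = (logit D − logit B) − (logit C − logit A).

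- Table 1: (−1.586 + 1.099) − (−1.099 + 0.619) = −0.487 + 0.480 = −0.007, odds ratio about 0.99. Effectively none.
- Pentoxifylline inert (A = C = 35%, B = D = 25%): 0 − 0 = 0, odds ratio 1. None.
- Complete antagonism (A = 35%, B = C = D = 25%): 0 + 0.480 = 0.480, odds ratio about 1.6. Strong.

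The last two scenarios have the same B and D, so B v D cannot tell them apart. Only C v A does.

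**Power by formula (uncorrected).** Power = Φ{[d − 1.960·√(2p̄(1−p̄)/n)] / √[(p₁(1−p₁) + p₂(1−p₂))/n]}.

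- B v D, 25% v 17%, n = 300: (0.080 − 0.0652)/0.0331 = 0.45, power 67%; about 60% at 256.
- A v B, 35% v 25%, n = 300: (0.100 − 0.0733)/0.0372 = 0.72, power 76%; about 70% at 256.
- Prednisolone margin with inert pentoxifylline, 35% v 25%, n = 600: (0.100 − 0.0519)/0.0263 = 1.83, power 97%; about 94% at 512.

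**Acting on the condition.** Assumed rule: if B v D is not significant at 5%, judge prednisolone by A v B; otherwise by the margin. Simulated without strata, at least 200,000 trials per scenario, at 256 to 300 per arm, uncorrected tests:

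| Scenario | B v D non-significant | Interaction test significant | Prednisolone power, margin | Prednisolone power, assumed rule |
|---|---|---|---|---|
| Pentoxifylline inert | 95% | 5% | 94-97% | 71-78% |
| Table 1 exactly true | 33-39% | 5% | see below | see below |
| Complete antagonism | 95% | 40-45% | 43-49% | see below |

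With inert pentoxifylline the loss is 97 − 78 = 19 points at 300 per arm and 94 − 71 = 23 points at 256.

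The other two rows were run under the rule with continuity-corrected tests. With Table 1 true, prednisolone power goes from 94.3% to 92.4% at 300 per arm and from 90.0% to 86.6% at 256. Under complete antagonism it rises, from 46.5% to 72.7% and from 40.6% to 65.4%.

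Pentoxifylline's type I error under the rule is about 6-6.5% uncorrected and about 5% with continuity correction.

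**The precedent.** Background gives the size of one of the two earlier studies: 70 patients. Assuming 35 per arm, power for 25% v 17% is about 13% uncorrected and 8% corrected. Its null result says little about interaction.

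**The case against.** The strongest reply is that this is a caveat in the Discussion and not an analysis rule. It says the assumption may be challenged, names no test, threshold or decision step, and leaves the margins in Statistical analyses untouched. A reader might infer that the trial would drop to four arms whenever pentoxifylline fails. The document does not support that. The four-arm consequence is worded firmly, but only once the assumption has been challenged, and how that is decided is not stated. The full protocol or analysis plan, not shown, may settle it.

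Second, the frequencies depend on how the condition is read. Background describes the earlier result as similar survival, 73.5% and 72.2%, a gap of 1.3 points. If the condition meant an observed B-D gap within 1.3 points, it would be met in about 26-27% of trials with inert pentoxifylline and about 2% under Table 1 (270 to 300 per arm). Non-significance is the more literal reading, because the text speaks of failing to demonstrate a difference. Even the narrower reading is met far more often than 5% when pentoxifylline is inert.

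Third, the article does not say which contrasts a four-arm analysis would use; A v B for prednisolone is an assumption. Under true antagonism, looking at simple effects is the better course, as the working shows.

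Fourth, Power calculation describes no interaction correctly, and if pentoxifylline alone is taken to work as in Table 1, D no better than B would indeed cast doubt on it. The Discussion sentence does not state that premise.

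These points limit the claim to what could happen. They do not rescue the reasoning, because a null B v D is still offered as grounds for doubting no interaction without reference to C v A.

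**Conclusion.** The point holds in this limited form: the Discussion names the wrong comparison as grounds for leaving the factorial analysis. A null B v D is equally compatible with an inert pentoxifylline and no interaction, with complete antagonism, and with chance.

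The figures of about 95% (inert pentoxifylline) and 33-39% (Table 1 true) assume that the condition means non-significance at 5%. The possible loss of 19 to 23 points further assumes that someone acts on it and that A v B then decides prednisolone. That loss belongs to prednisolone in the inert-pentoxifylline case; an inert drug has no power to lose. If Table 1 is true the prednisolone cost is only 2 to 3 points, and the type I error effect is minor. It would go too far to say that the plan contains a binding switching rule or that the trial as a whole would lose this power.

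**What to change.** Reword the factorial-design paragraph of the Discussion so that a null B v D result is not presented as evidence of interaction and does not by itself move the trial off the marginal comparisons in Statistical analyses. State that interaction will be judged from the prednisolone-by-pentoxifylline term in the stratum-adjusted logistic model, reported as an odds ratio with 95% confidence interval. Show the four arm-specific mortality rates and the simple effects (A v B, A v C, B v D, C v D) as supporting results.

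The cost is wording only: no extra patients or data. There is one small downside. The interaction test is weak, with about 40-45% power under complete antagonism, where power on the margins is only 43-49%. A non-significant term must therefore not be read as proof of no interaction, and the simple effects should be shown whatever its result.

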## Trial status

The trial is currently recruiting. Recruitment commenced on 1 February 2011 and will finish on 28 February 2014.

## Appendix A: Inclusion criteria

• Aged 18 years or older

• Clinical alcoholic hepatitis:

 - Serum bilirubin >80 μmol/L

- History of excess alcohol (>80 g/day male, >60 g/day female) to within 2 months of randomisation

• Less than 4 weeks since admission to hospital

• Discriminant function (DF)* ≥32

• Informed consent

• * DF = 4.6 × prothrombin time + (serum bilirubin (μmol/L) / 17.1) Prothrombin time (PT) = PT_PATIENT_ - PT_CONTROL_PT_CONTROL_ is defined as the midpoint value at each site; this mean value may be updated on a weekly or monthly basis.

## Appendix B: Exclusion criteria

• Abstinence of >2 months prior to randomisation

• Duration of clinically apparent jaundice >3 months

• Other causes of liver disease including:

◦ Evidence of chronic viral hepatitis (Hepatitis B or C)

◦ Biliary obstruction

◦ Hepatocellular carcinoma

• Evidence of current malignancy (except non-melanotic skin cancer)

• Previous entry into the study, or use of either prednisolone or PTX within 6 weeks of admission

• AST >500 U/L or ALT >300 U/L (not compatible with alcoholic hepatitis)

• Patients with a serum creatinine >500 μmol/L or requiring renal support

• Patients dependent upon inotropic support (adrenaline or noradrenaline). Terlipressin is allowed

• Active gastrointestinal bleeding

• Untreated sepsis

• Patients with known hypersensitivity to pentoxifylline, other methyl xanthines, or any of the excipients

• Patients with cerebral haemorrhage, extensive retinal haemorrhage, acute myocardial infarction (within the last 6 weeks) or severe cardiac arrhythmias (not including atrial fibrillation)

• Pregnant or lactating women
